### Primary outcome

HR-QoL will be measured by the 36-item Short-Form (SF-36).^28 29^ The SF-36 is widely reported as a subjective measurement of HR-QoL and includes 36 items that measure each of the following dimensions: physical role functioning, bodily pain, general health perception, vitality, social role functioning, emotional role functioning and mental health. The scores range from 0 to 100, where a higher score indicates better HR-QoL.

### Secondary outcomes

Dyspnoea will be assessed with the self-rated instrument, the Multidimensional Dyspnea Profile, which assesses sensory qualities of breathlessness, overall breathing discomfort and emotional responses. Each participant will be asked to identify and rate the activity that triggers maximal dyspnoea.^30^Fatigue will be assessed by the self-rating instrument for fatigue, the 9-item Fatigue Severity Scale. The scale provides separate scores for the physical, social and cognitive domains of fatigue, as well as a total combined measure of fatigue.^31^Symptoms of depression and anxiety will be assessed using the Hospital Anxiety and Depression Scale (HADS), which consists of two 7-item subscales. Items are scored between 0 and 3 according to how the respondent felt during the past week.^32^ An advantage of using HADS in the context of post COVID is its avoidance of questions on somatic symptoms, which may conflate reported levels of depression and anxiety.Cognitive function will be measured by using the Trail Making A+B test^33^ and the Verbal Fluency test.^34^ The tests are reliable measures of cognitive flexibility, attention span, visual search and processing speed; all domains discussed to be impaired by post COVID.^35^ Furthermore, the subjective measurement tool, Mental Fatigue Scale, will assess ‘brain fog’, mental fatigue and dysfunction. The scale consists of 15 items assessing general fatigue, stress, sensitivity and sleep.^36^Sleep quality will be assessed with the subjective measurement Pittsburgh Sleep Quality Index (PSQI). The 19-item scale measures seven domains; subjective sleep quality, sleep latency, sleep duration, habitual sleep efficiency, sleep disturbances, use of sleep medication and daytime dysfunction.^37 38^ The seven domains are then combined to a global score of sleep quality.Physical activity will be assessed with the short 4-item version of the International Physical Activity Questionnaire, a subjective self-report on vigorous, moderate and low physical activity.^39^Physical health measures include blood pressure (Omron M3 Comfort), resting heart rate, body mass index, grip strength (Vetek EH101), waist–hip ratio, blood oxygen levels (GIMA Pulse Oximeter OXY-3) after a sit-to-stand test, pulmonary function (COSMED microQuark spirometer) and heart rate variability (Actiheart V.5).Baseline measures will include demographic data of age, gender, education, residential status and employment status, alongside self-reported indicators of somatic health regarding the nature and duration of post COVID symptoms, comorbidities, medications, tobacco use and alcohol consumption.^40^

### Sample size

As there are no published RCTs of yoga for post COVID, the power estimate was based on data from our RCT of yoga-based exercise for well-being among physically inactive older adults,^41^ conducted in the same setting. A sample size of 35 participants per condition (yoga and health promotion intervention) would provide ~90% power (two-tailed α=0.05) to detect an effect size of 0.28 (small) on the primary outcome (SF-36). This equates to a postintervention group difference of ≥5 points (or ≥0.5 SD increase/improvement) on each of the two summary scores (mental and physical components). With an expected dropout rate of 20% and 1:1 allocation, the total number of participants estimated at baseline is 88.

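### The power statement equates an effect size of 0.28 with 0.5 SD, and its figure of about 90% does not follow from the inputs printed beside it

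*Protocol article*

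**What the plan says.** The Sample size section of the protocol article bases its estimate on the team's earlier yoga trial in inactive older adults. It claims that having 35 people in each arm "would provide ~90% power (two-tailed α=0.05) to detect an effect size of 0.28 (small) on the primary outcome (SF-36"). The next sentence converts that effect: "This equates to a postintervention group difference of ≥5 points (or ≥0.5 SD increase/improvement) on each of the two summary scores", meaning the mental and physical components. Twenty per cent dropout then gives 88 randomised. The section does not say whether 0.28 is a standardised mean difference or Cohen's f, and it names no test and no correlation between repeated scores.

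Two other sections bear on the reading. Follow-up assessments has the SF-36 taken at 6 weeks as well as at baseline and post intervention. Statistical methods plans a linear mixed model with group-by-time interactions, reported with Hedges' g, which is a standardised mean difference.

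**The concern.** Two different targets are presented as one, and a single power figure is attached to both. The contradiction shows before any power is calculated, because one SD cannot make 5 points equal to both 0.28 SD and 0.5 SD. The power figure then looks far too high for either target in a plain two-group comparison.

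What is at stake is how a null result will be read. The section tells readers that the trial has about nine chances in ten of detecting a small effect. If 0.28 is a standardised mean difference, the real chance is much lower at any moderate correlation, and a non-significant result would wrongly be taken as good evidence against a small benefit.

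**Working it through.** **Inputs, all from the Sample size section.** n = 35 per arm; alpha 0.05, two-sided; effect 0.28, said to equal 5 points or 0.5 SD; stated power about 90%; dropout 20%; total 88.

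**Dropout step.** 2 × 35 = 70; 70 / (1 − 0.20) = 87.5, rounded up to 88. This reproduces, so the difficulty lies in the effect size and the power.

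**Equivalence.** SD = difference / standardised effect.
- 5 points = 0.5 SD gives SD = 5 / 0.5 = 10, and then 0.28 SD = 2.8 points.
- 5 points = 0.28 SD gives SD = 5 / 0.28 = 17.9, and then 5 points is not 0.5 SD.

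**Attempt to reproduce about 90%.** Two independent groups, noncentral t with 68 degrees of freedom, noncentrality d × √(n/2), where √(35/2) = 4.183; critical value 1.995.
- d = 0.28: noncentrality 1.17, power 21%.
- d = 0.50: noncentrality 2.09, power 54%.
- With all 44 per arm analysed: 25% and 64%.

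The stated figure is not reproduced. For 90% power this comparison needs about 270 per arm at 0.28 SD or 86 per arm at 0.5 SD. With 35 per arm, the effect detectable with 90% power is 0.79 SD (7.9 points at SD 10).

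**Using the baseline score.** Let rho be the baseline to 12-week correlation. ANCOVA multiplies the SD by √(1 − rho²); a change score multiplies it by √(2(1 − rho)). The article gives no rho, so the values below are assumptions.

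| Target | Unadjusted | ANCOVA, rho = 0.5 | ANCOVA, rho = 0.7 |
|---|---|---|---|
| 0.28 SD | 21% | 27% | 37% |
| 0.50 SD | 54% | 66% | 82% |
| Effect detectable with 90% power | 0.79 SD | 0.68 SD | 0.56 SD |

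The last row is 0.786 × √(1 − rho²): 0.786 × 0.866 = 0.68 and 0.786 × 0.714 = 0.56.

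Solving for the rho that gives 90%, with target d:
- ANCOVA: rho = √(1 − (d/0.786)²), which is 0.77 for 0.5 SD and 0.93 for 0.28 SD.
- Change score: rho = 1 − (d/0.786)²/2, which is 0.80 for 0.5 SD and 0.94 for 0.28 SD.

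No single rho gives about 90% for both targets.

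**Reading 0.28 as Cohen's f.**
- For two equal groups d = 2f = 0.56. Power is 64% unadjusted and about 90% with ANCOVA at rho = 0.7.
- As a repeated-measures group-by-time interaction with N = 70 and two times, f = 0.28 gives 90.4% at correlation 0 and 97% to nearly 100% at correlations of 0.3 to 0.7. That f means a difference in change of 4 × 0.28 = 1.12 SD, or about 11 points at SD 10, not 5.

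**The case against.** The strongest defence is that 21% and 54% are not the power of the planned analysis. They belong to an unadjusted comparison at one time point, whereas the mixed model uses the baseline score. If the earlier trial showed a correlation of about 0.77 to 0.80, then 0.5 SD does have about 90% power. If 0.28 is Cohen's f, it corresponds to 0.56 SD, near the 0.5 SD in the text, and reaches about 90% at a correlation of 0.7. A condensed article may also leave the test and the correlation to the full protocol or the analysis plan.

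Much of this stands. A reader might infer that the statement is internally impossible, or that the trial's power is simply 21% or 54%. The documents support neither: the correlation is unknown, and about 90% is recoverable for 0.5 SD, or for an f of 0.28, under assumptions that the sponsor may hold. The missing test and correlation are not in themselves a fault of a condensed article.

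The printed contradiction remains. The f reading conflicts with the label 'small' (f = 0.25 is conventionally medium), with the figure of 0.5 SD (0.56 is not 0.5) and with the Hedges' g named in Statistical methods. A fuller document could supply the correlation, but it could not make 0.28 SD equal to 0.5 SD. No reading tried makes the whole statement consistent.

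**Conclusion.** The power statement contradicts itself and cannot be reproduced from what it prints. If 0.28 is a standardised mean difference, about 90% power for it would need a correlation of 0.93 to 0.94. That seems implausibly high for a quality-of-life score over 12 weeks, which is a judgement and not a figure in the documents. At correlations of 0.5 to 0.7, power for 0.28 SD is 27% to 37%. For 0.5 SD it is 66% to 82% over the same range, and about 90% only from roughly 0.77 to 0.80 upwards.

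These figures assume 35 analysed per arm, equal variances, one two-sided test at 0.05, and gain from the baseline score only. It is not established that the sponsor's calculation was wrong for whatever metric and correlation it used; what is wrong is the statement as printed.

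**What to change.** Keep 88 participants and rewrite the paragraph.

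- Remove the claim of about 90% power for a small effect of 0.28. Alternatively, state that 0.28 is Cohen's f, and correct both the label and the conversion to points and SD.
- State one target (5 points = 0.5 SD, SD 10), the test, and the assumed baseline to 12-week correlation with its source in the earlier trial.
- Give the power that follows for that target. Keep about 90% only if the supported correlation is about 0.77 (ANCOVA) or 0.80 (change score) or higher.
- Give the effect detectable with 90% power under the chosen correlation: 0.79 SD unadjusted, 0.68 SD at 0.5, about 0.56 SD at 0.7.
- Say that a null result would not exclude a small benefit.

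The cost is one reworded paragraph and possibly a less favourable stated power. No extra participants are needed.

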### Recruitment

Adults with post COVID aged 30–65 years will be recruited via an advertisement in a newspaper (Mitt-I) distributed free of charge throughout Stockholm. To support recruitment, a selection of general physicians in the Stockholm County region and a specialist COVID-19 clinic (Karolinska Hospital) will be provided with written information about the trial, which can be passed on to potential participants. The study will be briefly advertised as an opportunity to participate in a 12-week intervention for adults with post COVID. Participation in one of the two activities will be described: yoga or health promotion. Those interested in participating will contact a research assistant who will first conduct a brief screening over telephone, and then arrange a meeting to evaluate eligibility and perform baseline assessments.

### Randomisation and blinding

An independent statistician based at Karolinska Institutet will generate a sex-stratified randomisation list using a random number computer programme. The allocation sequence will be kept confidential and transferred into sealed envelopes by an administrator not involved in the study. Envelopes will be opened by the participants immediately following baseline assessments. Group allocation will be recorded on separate forms that are not available to follow-up assessors. Participants will be instructed not to discuss group allocation during follow-up appointments when a research assistant blinded to group allocation will be collecting data. Allocation will be kept confidential and only unblinded in the event of participant withdrawal or adverse events leading to ending participation.

### Data collection

#### Baseline assessment

The baseline assessment will be performed by trained research assistants prior to allocation. The assessment covers demographic data and the collection of primary and secondary outcomes, including anthropometric measurements, questionnaires and objective measurements (see Outcomes section). Baseline assessments are scheduled to take 60–90 min and are conducted daytime with a maximum difference of 3 hours. All questionnaire data will be collected using the REDCap software hosted on secure university servers requiring two-step authentication.^42 43^

#### Follow-up assessments

All participants will be followed up in person at half-time (6 weeks) to discuss progress, adherence and occurrence of any adverse events associated with the intervention. Assessments at 6 weeks will include the SF-36 and the PSQI. Postintervention assessments of all primary and secondary outcomes will be performed at 12+1 weeks, following the same procedure as at baseline (see figure 2). A brief semistructured interview is held at post intervention to gather participant views on the intervention. Postintervention assessments are held at the same time as baseline assessment for each participant.

**Figure 2 F2:**
[figure not shown]
Schedule of enrolment, interventions and assessments, according to SPIRIT guidelines.^26^ BMI, body mass index; BP, blood pressure; FSS, Fatigue Severity Scale; HADS, Hospital Anxiety and Depression Scale; HR-QoL, health-related quality of life; HRV, heart rate variability; IPAQ-SF, International Physical Activity Questionnaire Short Form; MDP, Multidimensional Dyspnea Profile; MFS, Mental Fatigue Scale; PSQI, Pittsburgh Sleep Quality Index; RHR, resting heart rate; SF-36, 36-item Short Form Health Survey; SPIRIT, Standard Protocol Items: Recommendations for Interventional Trials; TMT A+B, Trail Making test A+B; VF, Verbal Fluency; WHR, waist–hip ratio.

### Data management

Study participants will receive a unique study ID at inclusion. Collected data will be coded and kept confidential in participant case report forms using the same ID, which is considered source data. Source data will be transferred into electronic form and combined with questionnaire data collected in REDCap. Collected data will be handled only by authorised people and kept in a locked archive at the department of global public health, Karolinska Institute. The principal investigator is responsible for the maintenance and security of project data. A senior researcher not otherwise involved in the project will read the standard operating procedures and assess whether data collection and management have been followed correctly at 6 and 12 weeks.

### Statistical methods

A statistician not otherwise involved in the project will perform the analyses. The study collects quantitative data and intention-to-treat analyses will be performed to examine the effects of the yoga-based intervention compared with the health promotion. Missing data will be replaced using multiple imputations. Effects of the intervention will be explored using linear mixed modelling, where group-by-time interactions will be reported with regression coefficient estimates, CIs and effect sizes (Hedge’s g). As a secondary analysis, we will explore sleep as a potential mediator of the effects of yoga on HR-QoL. Sensitivity analyses will be performed, comparing imputed and non-imputed datasets. As ‘contamination’ effects are possible (eg, if health promotion participants decide to engage in yoga at their initiative), an ‘as treated’ analysis will be undertaken. Moderating effects of sex and age will be examined, as well as interaction effects of education on cognitive outcomes. All analyses will be carried out at study endpoint when data collection is completed.

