#### Health promotion (control)

Participants randomised to the health promotion group will receive fortnightly updates consisting of health promotion information (also for 3 months). A study-specific health promotion web page will be developed and updated with general health information; topics will include healthy eating, nature therapy, social connectedness, sleep habits and substance use (eg, strategies to quit smoking and reduce alcohol intake). Additional content will address post COVID concerns, providing practical guidance on managing fatigue, dyspnoea and ‘brain fog’. The contents will be concise (1–2 pages) and sourced from reliable organisations, including the WHO, and local health promotion agencies. An example of the health promotion content and format is available in online supplemental file 2. Participants will access the web page through a link sent fortnightly via email. To prevent group contamination, no health promotion information will be shared regarding breathing control, stretching or ‘mindfulness’ practices. Participants in the health promotion group will be advised not to take part in yoga, Pilates, tai chi or similar forms of exercise as well as any form of meditation during the 12-week intervention. Part of the rationale for delivering the health promotion to participants regularly is to reduce the likelihood of a Hawthorne effect, that is, to ensure the participants receive a similar level of attention. As an incentive, participants randomised to the health promotion group will receive a complimentary membership to the yoga studio when they attend their postintervention assessment.

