There are some unique challenges associated with this trial. Given that fatigue is a common symptom among patients with post COVID, some participants may find it challenging to complete the intervention, potentially leading to higher than predicted attrition rates. To reduce the risk of attrition bias, fortnightly phone calls to the yoga participants will be conducted, during which adherence and motivational issues will be discussed with a research assistant trained in cognitive psychology. Offering yoga memberships to participants in the health promotion group (following completion of the trial) serves as an incentive to complete the trial. Another potential challenge is the scheduling of classes to avoid conflicts with work or other commitments. To overcome this, classes will be offered at various times on weekdays, with the option to attend online on occasions when it is inconvenient to travel to the studio. However, participants will be encouraged to join onsite classes to gain the most benefit from the programme, especially during the first few weeks of the trial. A potential limitation is that the study lacks long-term follow-up, and thus, maintenance of intervention effects cannot be examined. Findings from the trial will be used to support grant applications for studies involving long-term assessments (12 months) and mechanistic effects of yoga in post COVID.

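### The one named missing-data check, imputed against non-imputed data, is unlikely to reveal outcome-dependent dropout; an arm-specific delta analysis should be added

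*Protocol article*

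**What the plan says.** All references are to the protocol article.

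- **Statistical methods, main analysis.** The article plans an intention-to-treat analysis. On missing values it says "Missing data will be replaced using multiple imputations", and on the model "Effects of the intervention will be explored using linear mixed modelling". It states neither the imputation model nor its assumption.
- **Statistical methods, sensitivity.** "Sensitivity analyses will be performed, comparing imputed and non-imputed datasets". In addition, "an ‘as treated’ analysis will be undertaken", but the stated reason for that is contamination of the control arm, not missing data.
- **Sample size.** "With an expected dropout rate of 20% and 1:1 allocation, the total number of participants estimated at baseline is 88". The dropout figure is not split by arm. The target is a 5-point difference, equated with 0.5 SD.
- **Discussion.** Fatigue is given as the reason why "some participants may find it challenging to complete the intervention, potentially leading to higher than predicted attrition rates". Attrition bias is named as a risk, and a retention measure is described for each arm: fortnightly calls for yoga, and a later studio membership for controls.
- **Interventions.** Yoga participants are encouraged to attend at least three classes a week. Controls receive a web link once a fortnight.
- **Follow-up assessments.** SF-36 and PSQI are repeated in person at 6 weeks in all participants.

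**The concern.** A sensitivity analysis for missing data is useful when it changes the assumption that cannot be tested. Here the doubtful assumption is MAR: given what was observed, those who leave would have scored like similar participants in the same arm who stayed. A mixed model fitted by likelihood to incomplete data relies on it, and so does multiple imputation in its usual form. Comparing the two mainly compares two ways of computing the same thing, and close agreement could be mistaken for evidence of robustness.

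This matters here because the primary outcome is self-reported quality of life, which includes vitality, and the article itself names fatigue as a possible cause of attrition. A participant who leaves because of worsening fatigue may have a lower unseen SF-36 than either analysis would predict. If that happens more in one arm, the estimated difference is biased, and the planned comparison would be unlikely to show it.

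**Working it through.** **1. The plan's own figure.** With 35 evaluable per arm and 20% dropout, 70 / (1 − 0.20) = 87.5, rounded up to 88, or 44 per arm. This reproduces the stated total. At 20%, about 0.20 × 44 = 8.8, or 9 participants per arm, would lack a final outcome. Since 5 points = 0.5 SD, the implied SD is 10.

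**2. Size of the possible bias.** Let p be the share missing in an arm. Let δ be the shortfall of its dropouts below their MAR prediction. Then

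corrected difference = MAR estimate − (p_yoga × δ_yoga − p_control × δ_control).

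The article gives neither δ nor p by arm, so both are assumptions. The 30%/10% split keeps the overall rate at 20%, since (30 + 10) / 2 = 20. Starting from an MAR estimate of 5 points:

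| Missing, yoga / control | δ | Shortfall in yoga dropouts only | Same δ in both arms |
|---|---|---|---|
| 20% / 20% | 5 | 5 − 0.20 × 5 = 4.0 | 5 − 0 = 5.0 |
| 20% / 20% | 10 | 5 − 0.20 × 10 = 3.0 | 5 − 0 = 5.0 |
| 30% / 10% | 5 | 5 − 0.30 × 5 = 3.5 | 5 − 0.20 × 5 = 4.0 |
| 30% / 10% | 10 | 5 − 0.30 × 10 = 2.0 | 5 − 0.20 × 10 = 3.0 |

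A shortfall of 10 points is a full SD. If p_control × δ_control is the larger product, the bias runs against yoga.

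**3. Would the planned comparison show it?** This was simulated with 1,500 trials per scenario, 44 per arm, SD 10, true effect 0, an assumed baseline-to-follow-up correlation of 0.6 and one follow-up. The shortfall was applied to yoga dropouts only. A baseline-adjusted analysis of observed cases stood in for the non-imputed mixed model. It was compared with standard MAR multiple imputation (20 imputations) using the same variables.

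| Missing, yoga / control | δ | Observed-case estimate | Imputed estimate | Mean absolute gap | False-positive rate (observed-case) |
|---|---|---|---|---|---|
| 20% / 20% | 0 | 0.00 | 0.00 | 0.15 | 5% |
| 20% / 20% | 5 | 0.95 | 0.95 | 0.16 | 7% |
| 20% / 20% | 10 | 2.02 | 2.02 | 0.15 | 18% |
| 30% / 10% | 5 | 1.52 | 1.53 | 0.16 | 13% |
| 30% / 10% | 10 | 3.01 | 3.02 | 0.16 | 33% |

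The bias grows as step 2 predicts, from 0 to about 3 points. The gap between the two methods stays at 0.15 to 0.16 points throughout. In this set-up the comparison carries no signal about outcome-dependent dropout.

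**The case against.** Several points on the other side have force.

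- **The article does not forecast unequal dropout.** A reader might infer that it predicts symptom-driven dropout concentrated in the yoga arm. It does not. The Discussion wording is conditional and names no arm, the 20% is a single figure, and both arms have a retention measure. Greater yoga dropout is only an inference from the difference in burden. This objection stands.
- **MAR is not stated.** It is inferred from the default form of both methods. An imputation model can also use variables that an SF-36 mixed model would leave out, such as baseline fatigue, HADS, dyspnoea, 6-week PSQI and attendance. The two results could then differ, and the difference would be informative about measured predictors of dropout. The simulation used baseline only, so its near-identity belongs to that set-up. It would be too strong to say that the two must coincide whatever the bias. This stands. Even then, the comparison tests only what was measured.
- **Fatigue-related dropout may be partly MAR.** Baseline fatigue and the 6-week SF-36 and PSQI can explain some of it. Those who stop classes can also still be assessed under intention-to-treat, so non-completion of yoga is not the same as a missing outcome. This stands and reduces the likely bias by an unknown amount.
- **Detail may sit in an analysis plan that is not shown.** That plan may add an analysis that departs from MAR, so no claim is made that none exists. But the article itself specifies this comparison as the missing-data check, so its limits can fairly be raised.

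**Conclusion.** The point holds in a conditional form. With standard multiple imputation and a likelihood-based mixed model on similar variables, the named comparison cannot show whether the result is robust to outcome-dependent dropout. The article's own concern about fatigue and attrition bias makes that question relevant.

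The size cannot be fixed from the document. If 20% are missing in the yoga arm and only those participants fall short by 5 or 10 points, a 5-point estimate becomes 4.0 or 3.0. With equal dropout and equal shortfall in both arms, it stays at 5. A reader might take the lower figures as the expected effect of the trial; they are scenarios and not forecasts. Nor does the point make the primary analysis wrong, since MAR is a reasonable starting assumption. What is missing from the stated check is a measure of how far that assumption can fail before the conclusion changes. This is an inexpensive improvement, not a fatal flaw.

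**What to change.** Keep the primary analysis and the planned imputed versus non-imputed comparison, and add the following before the data are analysed.

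1. State that the imputation assumes MAR. Include baseline symptom scores (fatigue in particular) and the 6-week SF-36 and PSQI in the imputation model. With 44 per arm, the set of added variables should stay small.
2. Add a pre-specified delta-adjusted (tipping-point) analysis of the SF-36. Shift the imputed 12-week values by a delta varied separately in each arm, including equal shifts in both arms. Justify the range of deltas against the 5-point target.
3. Report the combinations of deltas at which the conclusion changes, together with the number missing and the reasons by arm.

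Reference-based imputation, in which yoga dropouts are imputed from the control arm, is an optional alternative.

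The cost is a few lines of text and some extra code, with no new data. The downside is a little more analysis work and possibly a less favourable statement on robustness.
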